## Abstract

**Background:**

The Prevention of Overweight in Infancy (POI) study was a four-arm randomised controlled trial (RCT) in 802 families which assessed whether additional education and support on sleep (Sleep group); food, physical activity and breastfeeding (FAB group); or both (Combination group), reduced excessive weight gain from birth to 2 years of age, compared to usual care (Control group). The study had high uptake at recruitment (58 %) and retention at 2 years (86 %). Although the FAB intervention produced no significant effect on BMI or weight status at 2 years, the odds of obesity were halved in those who received the sleep intervention, despite no apparent effect on sleep duration. We speculate that enhanced self-regulatory behaviours may exist in the Sleep group. Self-regulation was not measured in our initial intervention, but extensive measures have been included in this follow-up study. Thus, the overall aim of the POI follow-up is to determine the extent to which augmented parental support and education on infant sleep, feeding, diet, and physical activity in the first 2 years of life reduces BMI at 3.5 and 5 years of age, and to determine the role of self-regulation in any such relationship.

**Methods/design:**

We will contact all 802 families and seek renewed consent to participate in the follow-up study. The families have received no POI intervention since the RCT finished at 2 years of age. Follow-up data collection will occur when the children are aged 3.5 and 5 years (i.e. up to 3 years post-intervention). Outcomes of interest include child anthropometry, body composition (DXA scan), diet (validated food frequency questionnaire), physical activity (accelerometry), sleep (questionnaire and accelerometry), and self-regulation (questionnaires and neuropsychological assessment).

**Discussion:**

Our follow-up study has been designed primarily to enable us to determine whether the intriguing benefit of the sleep intervention suggested at 2 years of age remains as children approach school age. However, cohort analyses will also investigate how BMI, self-regulation, and sleep consolidation develop during the early years. This information will be valuable to researchers and policy makers progressing the field of early childhood obesity prevention.

**Trial registration:**

ClinicalTrials.gov number NCT00892983.

## Background

Globally, it is estimated that 42 million children are overweight or obese, illustrating the seriousness of this public health challenge [1]. The prevalence of childhood obesity has increased substantially since the 1970s and there is little evidence to suggest these rates are tapering off [2, 3]. It is clear that New Zealand (NZ) children are following this global trend, with 9.5 % of children being obese by the time they are only 2–4 years of age and a further 20 % being overweight [4]. In addition to the immediate adverse effects of obesity in infancy and toddlerhood [5], it is also a strong risk factor for overweight later in life, and the associated health effects [6]. Determining the most effective tools for reducing excessive weight gain early in life is paramount if we are to prevent obesity before it becomes entrenched [7].

The early years are a time of immense change when fundamental behaviours including those around eating, sleeping, and physical activity are established. It is apparent that overweight and obesity develop from the complex interaction of multiple factors [8, 9], including biological effects (e.g. genetic susceptibility [10], and an ‘obesogenic’ gut microbiome [11]), behavioural factors (e.g. dietary, physical activity, sedentary and sleep habits [12, 13]), as well as cultural, social, environmental and economic influences [14, 15]. Evidence also suggests that parenting and discipline practices [16–18], mental health [19], and infant temperament [20, 21] may influence the development of obesity in young children. It has recently become apparent that many of these factors are influenced by self-regulation – the ability to control one’s behaviour without external assistance [22, 23]. To gain traction in reducing childhood obesity rates, interventions need to modify a wide range of these factors.

Relatively few obesity prevention trials have been undertaken in the first 2 years of life [24, 25], and many have been small [26, 27] or used non-randomised designs [28, 29]. However, three large randomised controlled trials (RCTs) have recently been undertaken in Australia. All three have targeted nutrition and eating behaviours in families [30–32] with two also addressing physical activity and sedentary behaviour [30, 31]. However, only one of these studies saw benefits in terms of relative body weight at the end of the trial [30]. This home-based intervention in mothers from disadvantaged areas of Sydney reported body mass index (BMI) values to be 0.29 kg/m^2^ (95 % confidence interval −0.55 to −0.02; *P* = 0.04) lower in intervention compared with control children at 2 years of age, with differences observed in several behavioural variables that might explain this effect on weight status [30]. Disappointingly, this intervention benefit was only transient, with significant effects no longer apparent when the children were 5 years of age [33]. Neither of the remaining studies observed a significant intervention effect on BMI at 18 [31] or 24 [32] months of age, nor at follow-up at 5 years of age [34]. Interestingly, all three studies had little impact on nutritional intake or levels of physical activity in children, although time spent watching television appeared to be modifiable [30, 31, 35]. Although it is not clear why it might be so difficult to influence nutrition or activity levels early in life, it is feasible that other priorities such as infant crying [36] and sleep problems [37] are more important to parents at this age.

In 2009, we commenced the POI (Prevention of Overweight in Infancy) RCT in 802 Dunedin families designed to reduce the number of children with excessive weight gain in the first 2 years of life [38]. Participants were randomised to one of four groups: Control (usual care), FAB (food, physical activity and breastfeeding), Sleep, or Combination (received FAB and Sleep interventions). All four groups received standard Maternity and Well Child care [39], and the three intervention groups received additional guidance and support on the relevant behaviours (breastfeeding, diet, physical activity, sleep) as detailed previously [38, 40, 41]. The POI study, and the three large controlled trials from Australia (Healthy Beginnings [42], Nourish [43], and InFANT [44]), are combining their data to form a prospective meta-analysis of the feasibility and effectiveness of early obesity prevention efforts (Early Prevention of Obesity in Children, EPOCH) [45]. Care has been taken to ensure that the study design, participants, intervention, comparators and outcome measures are similar across all four studies.

All four EPOCH studies aimed to modify BMI in the first 2 years of life through food, parenting and physical activity interventions. However, in addition to targeting these behaviours, the POI study also included a sleep intervention arm. Whether sleep interventions can affect growth trajectories is not known, but is an area of great interest internationally [46]. We know that adequate sleep in infancy and childhood is important for behaviour, learning and family functioning [47] but a wealth of data now link poor sleep habits with an increased risk of overweight in childhood as well [13, 48–50]. Despite this, we know relatively little about whether it is possible to change sleep behaviour and ultimately affect growth because very few sleep interventions have been published to date [26, 51–53]. Our brief POI intervention (2 core visits) focused on developing appropriate sleep habits from birth, including the ability of the infant to regulate their own sleep, i.e. to fall asleep when tired without external aids such as being fed to sleep or being rocked in a parent’s arms [54]. At 2 years of age, we observed no significant intervention effect on mean BMI across the four study groups. However, an exploratory analysis demonstrated that when the two groups receiving the sleep intervention (Sleep and Combination) were combined, the sleep intervention halved the odds of obesity (BMI ≥95th percentile) compared to the groups who did not receive the sleep intervention (Control and FAB) [55]. It thus seems opportune to follow-up this cohort to determine, first, whether this effect on obesity is sustained, and second, the mechanism by which a sleep intervention might beneficially affect weight in young children.

While it is clear that sleep is related to body weight in children [13, 48–50] the mechanisms are poorly understood [56]. The development of self-regulation, which mainly occurs in the first 4 years of life, seems fundamental in setting an individual’s life trajectory [57] and it appears that some of the earliest demonstrations of self-regulation are the ability to go to sleep without external assistance, and to match energy intake with energy requirements. Infants who are able to regulate their own sleep have healthier sleep-wake patterns later in life [58], and general measures of self-regulation have also been associated with healthier body weights in children [59–61]. How infants regulate their own sleep is difficult to measure by questionnaire, and objective measurements using video-cameras are not feasible in large trials [62]. However, we have included well-validated measures of general and sleep self-regulation in the follow-up study proposed here. Child measures of inhibitory control and language (core skills associated with self-regulation) will be assessed using the Developmental Neuropsychological Assessment (NEPSY) subsets of statue, comprehension, phonological processing, and word generation [63], and the Head-Toes-Knees-Shoulders task [64], a measure of behavioural regulation which also assesses inhibition. These findings will be augmented with age-appropriate measures of the self-regulation of sleep (self-settling to sleep, awakenings from sleep, consolidated sleep duration), and energy balance (dietary intake, parental beliefs about the child’s ability to regulate their own energy intake, and physical activity assessed using accelerometry).

Other factors of interest in child growth include physical activity, diet and the gut microbiota. How physical activity patterns develop is of interest given the low rates of physical activity seen in some [65, 66], although not all [67], studies in young children, and the observation that marked declines in activity are apparent even in the preschool years [68]. Accelerometers are increasingly being used to measure physical activity in children under five years of age [69], although rarely in those less than 3 years of age [70, 71]. 24-h accelerometry data (over 5 days) were collected at 6, 12 and 24 months as part of POI to measure both sleep and physical activity [72], and extending these measures in our follow-up study will allow us to examine multiple questions of interest regarding the early development of physical activity and inactivity and sleep. How the gut microbiota develop in early life and the potential relationship with obesity is of intense interest worldwide [73]. Despite clear differences in bacterial composition between lean and obese mice, corresponding findings in studies of humans have been considerably more mixed [74–76]. However, several longitudinal studies have now demonstrated that variation in gut microbiota during infancy is related to overweight status at older ages [77–79], although existing studies contain few subjects [77, 78] or use parent-reported BMI values [79] which have known inaccuracies [80]. Many studies are also unable to account for dietary intake, which clearly alters the bacterial composition of the microbiome [76]. Although it remains to be seen whether variation in gut microbiota is a cause or consequence of obesity [81], our prospective study includes a large number of children whose diet and lifestyle since birth has been well documented.

The overall aim of the POI follow-up is to determine the extent to which augmented parental support and education on infant sleep, feeding, diet, and physical activity in the first 2 years of life reduces BMI at 3.5 and 5 years of age, and to determine the role of self-regulation in any such relationship.

The key objectives are to determine whether the POI ‘Sleep intervention’ or ‘FAB intervention’ from late pregnancy to 2 years of age result in differences in:BMI z-score at 3.5 and 5 years of age (primary objective)Self-regulation (overall, sleep-related, or energy) at 3.5 and 5 years of ageOther weight indices (BMI, prevalence of overweight or obesity, waist circumference) at 3.5 and 5 years of ageBody composition at 5 years of ageSleep (timing, duration, awakenings, problems) at 3.5 and 5 years of agePhysical activity at 3.5 and 5 years of ageDiet at 3.5 and 5 years of age.

Additional objectives include determining, in a cohort analysis, possible predictors of BMI, self-regulation (overall, sleep-related, energy), and sleep consolidation (timing, duration, awakenings, problems) at 3.5 and 5 years of age.

## Methods/Design

### Study design and participants

The POI study was a four-arm RCT controlled trial assessing whether additional education and support on sleep (Sleep group); breastfeeding, diet, and physical activity (FAB group); or both (Combination group) reduced excessive weight gain from birth to 2 years of age compared to usual care (Control group) [38]. All mothers who had booked into the single maternity hospital (>97 % of all births) serving the city of Dunedin, NZ, between May 2009 and November 2010 were invited to participate in the POI study when they were 28–30 weeks gestation. Exclusion criteria applied before birth were: home address outside Dunedin, planning to move from Dunedin in the next 2 years, booked into the maternity centre after 34 weeks gestation, or unable to communicate in English or Te Reo Māori (language of the indigenous (Māori) ethnic group of NZ). Exclusion criteria applied after birth were: identification of a congenital abnormality likely to affect feeding or growth, or birth before 36.5 weeks gestation. All participants enrolled in the original POI intervention will be invited to participate in follow-up measurements by research staff. The study was approved by the University of Otago Human Ethics Committee (12/274) and written informed consent will be obtained from participants before commencing the first follow-up visit at 3.5 years of age.

### Sample size

Retention at 2 years was 86 % (*n* = 686/802) which is higher than was anticipated in our original power calculations (20 % loss to follow-up was assumed) [38]. Based on this, we anticipate retaining at least 75 % of the original cohort through to age five, giving us an estimated sample size at 5 years of at least 600 participants. This would provide 80 % power to detect a difference in BMI of 0.3 kg/m^2^ or larger at 5 years of age between any pair of the four groups using a two-sided test at the 0.05 level, based on earlier data from this research group suggesting a standard deviation of 0.8 [49]. This sample size would also allow 80 % power for detecting differences in self-regulation scores of 0.35 standard deviations between any two arms of the trial (falling between a “small” and “moderate” effect size) and detecting correlations at the study level of 0.12 or larger between continuous measures (e.g. between parenting style at 12 months and self-regulation at 5 years and between consolidated sleep hours at 6 months, and self-regulation at 3.5 and 5 years) using two-sided tests at the 0.05 level.

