### Analysis

For the key objectives, data will be analysed using linear, logistic (binary or ordinal), and Poisson (or negative binomial) regression models to compare the four arms of the trial in terms of continuous, categorical (binary or ordinal), and count outcomes respectively, with a random effect for participant along with terms for age and a group-by-age interaction added when longitudinal outcomes are analysed. As analyses at 2 years did not find consistent evidence in support of interactions between the Sleep and FAB interventions, we also plan to investigate outcomes using combined Sleep and combined FAB groups. A two stage process will be used, first investigating whether there is evidence for such an interaction (a reparameterisation of the four group model) and if not, the Sleep and FAB intervention terms will be investigated without the interaction included, although this process will increase the Type I error rates beyond the nominal level [101]. All *P*-values will be reported using three decimal places and *p*-values less than 0.001 will be reported as ‘*p* < 0.001’. Two-sided *p* < 0.05 will be considered to indicate statistical significance and no adjustments for the multiple outcomes are planned. Post-hoc comparisons between the three intervention and one control groups will only be performed where the overall (Wald) test is statistically significant. Where available, baseline values will be included in models and all models will include the stratification variables [102]. Standard model diagnostics will be used and log-transformations used where this improves residual normality and/or homoscedasticity for continuous outcomes. Homser-Lemeshow tests will be used for binary logistic regression models and proportionality will be assessed in ordinal logistic regression models using generalised ordinal logistic regression. Overdispersion will be examined using a likelihood ratio test for count outcomes, with negative binomial regression used when this is significant. Where model residuals remain unacceptable for continuous outcomes, quantile regression, including mixed quantile regression where appropriate, will be used instead to model medians.

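### The sample-size inputs give about 90% pairwise power for 0.3 kg/m², not 80%, and the calculation covers neither the named primary outcome nor the planned tests

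*Protocol article*

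**What the plan says.** The Sample size section starts from retention: "we anticipate retaining at least 75 % of the original cohort through to age five", giving "an estimated sample size at 5 years of at least 600 participants". It then claims "80 % power to detect a difference in BMI of 0.3 kg/m^2^ or larger at 5 years of age", for a comparison "between any pair of the four groups using a two-sided test at the 0.05 level". The SD is "based on earlier data from this research group suggesting a standard deviation of 0.8". The same sample size is said to give 80% power for 0.35 SD in self-regulation scores between two arms, and for a correlation of 0.12 across the study.

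Three other places bear on this:

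- **Key objectives (end of Background).** BMI z-score at 3.5 and 5 years is the primary objective. Raw BMI is listed among the other weight indices.
- **Outcome measures, Table 1.** BMI is assigned to objective a, the primary one, and BMI-for-age z-score to objective c.
- **Analysis.** A four-arm model comes first. "Post-hoc comparisons between the three intervention and one control groups will only be performed where the overall (Wald) test is statistically significant". The section also plans to analyse combined Sleep and combined FAB groups if there is no evidence of interaction.

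**The concern.** The article's only power statement should follow from its inputs and refer to the outcome and tests that will be used. Here the stated power does not match the inputs. The outcome powered is not the one the objectives call primary. The test powered is a free-standing two-arm comparison, whereas the plan has an overall test followed by pairwise comparisons, plus pooled contrasts.

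What is at stake is how a null result is read. The cohort is already randomised and all 802 families are invited, so recruitment does not depend on this paragraph. A reader who uses it to judge which differences the follow-up could detect has the wrong figure for the stated comparison, and no figure for the z-score or for the pooled sleep contrast. The pooled sleep contrast is the one that produced the 2-year obesity finding which motivates the study.

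**Working it through.** **Inputs.** From Sample size: 802 × 0.75 = 601.5, stated as at least 600; SD 0.8; difference 0.3 kg/m²; two-sided 0.05. The article does not state the allocation ratio. Equal allocation is assumed, so n = 150 per arm.

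**1. The stated figure.**

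- SE of a pairwise difference = 0.8 × √(2/150) = 0.0924.
- 0.3 / 0.0924 = 3.248.
- Power = Φ(3.248 − 1.960) = Φ(1.288) = 90.1% (89.9% with the t distribution). The stated 80% is not reproduced.
- Detectable at 80%: (1.960 + 0.842) × 0.0924 = 0.259, or 0.26 kg/m².
- n per arm for 0.3 at 80%: 2 × (2.802 × 0.8 / 0.3)² = 111.6, or 112 (113 with the t distribution).
- SD at which 150 per arm gives exactly 80% for 0.3: 0.3 / (2.802 × √(2/150)) = 0.93.

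**2. The companion figures at n = 600.**

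| Quantity | Stated at 80% | Detectable at 80% | Power at stated value |
|---|---|---|---|
| BMI, pair | 0.3 kg/m² | 0.26 kg/m² | 90% |
| Self-regulation, pair | 0.35 SD | 0.32 SD | 86% |
| Correlation | 0.12 | 0.114 | 84% |

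The second row uses 2.802 × √(2/150) = 0.3235. The third uses tanh(2.802 / √597) = 0.114. Each stated value is the n = 600 value rounded upward.

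**3. Could an unstated correction explain 80%?** Bonferroni for three comparisons (0.05/3) gives 80.3% for BMI. However, the text states 0.05 and any pair, which is six pairs; correcting for six gives 72.9%. The three-comparison correction also gives only 73.8% for the 0.35 SD claim. It does not explain the paragraph.

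**4. The gated test.** Joint power is the probability that the 3-df overall test and the pairwise test are both significant. It was simulated with 150 per arm, SD 0.8 and the two compared arms 0.3 apart.

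| Pattern of the four means | Overall test | Overall and pairwise |
|---|---|---|
| Only one arm differs (0, 0, 0, 0.3) | 93% | 87% |
| Other two arms midway (0, 0.15, 0.15, 0.3) | 78% | 78% |

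**5. The pooled contrasts.** With 300 versus 300, the 80% detectable difference is 2.802 × √(2/300) = 0.229 SD, which is 0.18 kg/m² at SD 0.8. Power for 0.3 kg/m² is 99.6%.

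**6. Sensitivity to the SD (assumed values), difference 0.3 kg/m².**

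| SD | Pairwise, 150 v 150 | Pooled, 300 v 300 |
|---|---|---|
| 0.8 | 90% | 99.6% |
| 1.0 | 74% | 96% |
| 1.2 | 58% | 86% |
| 1.5 | 41% | 69% |

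**7. The z-score.** The article gives neither an SD nor a target difference for BMI z-score, so power for that outcome cannot be computed from it.

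**The case against.** The strongest defence is that the paragraph is cautious. It speaks of 0.3 or larger and of at least 600, which is the language of bounds, and all three quoted values are the n = 600 values rounded up. This stands: the error understates power, and no participant number depends on it. A reader might infer from the differing powers that the three figures came from three different sample sizes. The document does not support that, because upward rounding from one n of 600 explains them all.

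On the outcome, the overall aim speaks of BMI and Table 1 puts BMI under the primary objective, so raw BMI may have been intended. That is fair, and it means the z-score cannot simply be presumed right. It leaves an inconsistency to settle.

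On the gate, the loss depends on the pattern of means, and in one of the two patterns power stays above 80%. The Analysis wording might also allow comparisons among all four groups, but the gate applies on either reading. A condensed article may also leave power for further contrasts to a fuller plan. This weakens the complaint about the pooled contrasts, although the article does state power for a test it does not plan to run ungated.

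A stronger reading is tempting on the SD. The Background passage beginning "This home-based intervention in mothers from disadvantaged areas of Sydney reported body mass index (BMI) values to be" gives a confidence interval of −0.55 to −0.02, so SE = 0.53 / 3.92 = 0.135. With two equal groups, SD = SE × √N / 2, and an SD of 0.8 would imply about 140 children in a trial described as large; N = 300 would imply 1.17. A reader might conclude that the cited evidence contradicts 0.8. It does not establish that. The trial is in another population, at age 2, with no N or SD given, and the source of the 0.8 is the group's own earlier data, which is not shown. This supports a sensitivity range and nothing stronger.

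Finally, all effects will carry 95% confidence intervals used to judge clinical significance, so a null result need not be read from the power sentence alone. That limits the harm.

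**Conclusion.** The point holds in a limited form. On the stated inputs, pairwise power for 0.3 kg/m² is about 90%, and 80% power corresponds to 0.26 kg/m², assuming equal arms of 150. The mistake is in the safe direction. It does not show an underpowered study, and a claim that real power is well below 80% would rest on SDs the document does not give for this cohort.

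The mismatch with the plan matters more. The objectives, the Sample size section and Table 1 disagree on whether BMI or BMI z-score is primary, and the z-score has no power basis. At SD 0.8 the gated pairwise test has about 78% to 87% power for 0.3 kg/m² in the two patterns tried, against 90% ungated. The pooled contrasts are well powered (0.18 kg/m² detectable at SD 0.8), but the article does not say so.

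**What to change.** 1. Decide whether BMI or BMI z-score is primary, and make the key objectives, the Sample size section and Table 1 agree.
2. Restate the power for that outcome. If BMI is kept: 90% for 0.3 kg/m², or 0.26 kg/m² at 80%, with 150 per arm and SD 0.8. If z-score is primary: give its SD and a target difference, and compute from those. State the allocation assumed.
3. Give the companion figures on the same basis (0.32 SD and r = 0.114 at 80%), or say that they are rounded up.
4. Add the pooled Sleep and FAB contrasts (0.23 SD at 80% with 300 versus 300), and state what the Wald gate does to pairwise power, with the pattern of means assumed.
5. Show sensitivity to a larger SD, for example 74% pairwise power at SD 1.0. The team's own data at 2 years can inform the range, with two cautions: 686 is the number retained, not necessarily the number with BMI measured, and the SD at 2 years need not equal that at 5.

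The cost is one rewritten paragraph and a correction to the objectives or to Table 1. No extra enrolment or data collection is needed. Some figures will look less favourable if the SD proves larger than 0.8.
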